## Discussion

Long COVID syndrome is a clinical condition characterized by the persistence of symptoms for at least 12 weeks after the onset of COVID-19. While its manifestation can vary greatly in terms of intensity and frequency, some of the most common symptoms include respiratory problems, myalgia, extreme fatigue, moodiness, cognitive impairment, and difficulty sleeping [65, 66]. This study protocol presents the design of an RCT with the primary objective of evaluating the effectiveness of an AIR + Mindfulness intervention, in comparison to a relaxation therapy program, for enhancing the health-related quality of life in patients diagnosed with Long COVID. Given the global impact of this syndrome, there has been a notable increase in scientific interest for the development and evaluation of different intervention strategies aimed at improving the health status of these patients. Indeed, certain psychological interventions, such as AIR and mindfulness have demonstrated positive outcomes in alleviating psychological distress for Long COVID [26]. However, the evidence remains limited, and further research is necessary to replicate and expand upon these findings [28, 29].

Despite the promising results to date, there is currently no medical and/or psychological treatment with sufficient empirical evidence that enables effective management of the symptoms of Long COVID syndrome [10, 67]. Given that scientific research suggests that the symptoms of Long COVID are due, albeit partially, to immune dysregulation and chronic inflammation in the body [1, 3], the hypothesis presented in this paper is that the AIR + Mindfulness program will effectively benefit these patients. This belief is grounded in its demonstrated efficacy in conditions of a comparable nature, such as fibromyalgia and CFS, by influencing processes that impact the immune system, such as reducing levels of C-reactive protein and brain-derived neurotrophic factor, which are considered a key element in a variety of neuroplasticity processes such as pain modulation, nociception, and hyperalgesia [9, 13, 22, 68].

The study has several strengths. First, this is the first RCT to be conducted in Spain that applies a psychotherapy program for the management of symptoms derived from Long COVID. Secondly, owing to the little scientific evidence currently available in the field, the results obtained will be of great value for the process of designing and developing effective intervention programs to manage this syndrome. Third, in addition to the post-treatment evaluation, a follow-up will be carried out three months after the end of the intervention program, which will allow its medium-term effects to be evaluated. The fact that the intervention is delivered in a group format can generate a context in which the participants’ involvement is promoted, favoring greater adherence and, consequently, greater benefits. Finally, an active control group will be used, as recommended in research using contemplative programs [69], as it allows possible changes in the variables to be attributed to the intervention and not only to other factors, such as the attention shown by the instructor or the relationship with the group.

With regard to the potential limitations of the study, it should be noted that the intervention will be conducted solely in the city of Zaragoza (northeastern Spain), without the possibility of extending the study area. Therefore, the generalizability of the results will be limited. Other potential difficulties may be that since patient participation in the study will be voluntary, there could be a higher dropout rate due to unforeseen life circumstances or health-related conditions. Finally, all the variables evaluated will be collected only through self-report questionnaires; thus, all data collected will have the limitations of this particular methodology.

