### Sample size

According to a previous study, when use of the AIR + Mindfulness intervention was compared to a similar active control group (i.e., relaxation therapy) on a sample of fibromyalgia patients, it demonstrated an overall improvement in the severity of the disorder––measured using the Fibromyalgia Impact Questionnaire Revised [32], a tool that evaluates the effect of this condition on a person’s wellbeing and quality of life, considering pain levels, physical functioning, sleep quality, fatigue, mood, and the impact of the condition on daily activities––with a moderate effect size (d = 0.60) at post-intervention [22]. Assuming a similar effect size in terms of quality of life on Long COVID symptomatology at post-intervention, in order to detect this difference with an overall α level of 5% and a statistical power set at 80% in two-tailed tests, 42 patients per group are required. Given that a dropout rate of around 15% of the participants is expected [33], the sample size will be increased until the number of 50 participants is achieved per group at the beginning of the study.

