Mindfulness training of is associated with increased cortical thickness in the anterior insula (involved in interoception, affected by fibromyalgia and chronic fatigue) and the frontal cortex (involved in the integration of emotions as fear and cognition process). Moreover, this technique seems to change cognitive evaluations of what is considered a threat, decrease reflective thinking, and reduce stress. Mindfulness can also directly increase positive states of arousal [37–39]. Thus, the practice of mindfulness seems to reinforce the AIR intervention, given that the activity of the amygdala has been seen to decrease with its practice, as well as activation of the prefrontal cortex, an area also involved in diminishing the fear conditioning response.

Previous studies suggest that the practice of mindfulness causes effective and lasting results for the symptomatology and underlying pathology of post-viral fatigue, such as Long COVID. It has been found to reduce fatigue and unrefreshing sleep, and for those with post-viral infections, to improve immunity and reduce pathogen-driven inflammation [40, 41].

The intervention will be administered by a clinical psychologist who is trained in and has experience in facilitating groups for both the AIR program and mindfulness-based interventions. The content of each session is described in Table 1.

**Table 1 Tab1:** AIR + Mindfulness program

Session 1	Overview of the retraining and mindfulness course. Introduction to the course. Goals. Work method. Developing a regular mindfulness practice. Mindfulness practices. Guidelines for the regulation of the nervous system. Thought diary. 3-minute mindfulness practice. Health visualization.
Session 2	Hypothesis on the origin of Long COVID. Theoretical aspects. The amygdala-insula-limbic hypothesis on how stress activates the nervous system. Conditioning and reconditioning, and health visualization. Breathing meditation.
Session 3	Main technique of reeducation of the amygdala and the insula. Reconditioning. Learning to break physical activations caused by stimuli and symptoms. Patterns, meanings, and unconscious negative emotions. Somatic responses in the body. Guidelines for establishing a daily practice. Body scan meditation.

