#### Relaxation intervention

The program for the active control group includes progressive muscle relaxation training, as proposed by Bernstein and Borkovec [42], with the addition of visualization and breathing practices. The intervention will be administered by a clinical psychologist who is experienced with groups and is trained in relaxation therapy. The sessions contained in this program are described in Table 2.

**Table 2 Tab2:** Relaxation program

Session 1	Presentation of the group and the relaxation objectives. Basic principles of progressive muscle relaxation. Brief explanation of the initial procedure with 16 muscle groups. Progressive muscle relaxation practice with 16 muscle groups. Identifying the sensations of and difficulties with relaxation.
Session 2	Sharing homework-related experiences and doubts. Imagination training and visualization techniques. Practice of progressive muscle relaxation with 16 muscle groups. Identifying the sensations of and difficulties with relaxation.
Session 3	Sharing homework-related experiences and doubts. Brief explanation of the procedure with 7 muscle groups. Practice of progressive muscle relaxation with 7 muscle groups. Visualization practice: orange. Identifying the sensations of and difficulties with relaxation.
Session 4	Sharing homework-related experiences and doubts. Practice of progressive muscle relaxation with 7 muscle groups. Visualization practice: the beach. Identifying the sensations of and difficulties with relaxation.
Session 5	Sharing homework-related experiences and doubts. Brief explanation of the procedure with 4 muscle groups. Practice of progressive muscle relaxation with 4 muscle groups. Visualization practice: the landscape. Visualization practices: the globe. Identifying the sensations of and difficulties with relaxation.
Session 6	Sharing homework-related experiences and doubts. Brief explanation of relaxation by evocation, relaxation by evocation + counting, and relaxation by counting. Relaxation by evocation. Mental relaxation and visualization practice: the perfect day. Identifying the sensations of and difficulties with relaxation.
Session 7	Sharing homework-related experiences and doubts. Explanation of relaxation techniques through breathing. Breathing practice: count, lengthen, hold. Visualization: the ray of light. Identifying the sensations of and difficulties with relaxation.

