## Data analysis plan

The distribution of the sociodemographic and clinical variables will be presented by frequencies (percentages), medians (interquartile range, IQR) or means (standard deviations, SD), according to their level of measurement and statistical distribution.

The primary analysis will consist of a comparison between AIR + Mindfulness (intervention arm) and relaxation therapy (control arm) at post-intervention, considering the quality-of-life main outcome (SF-36) as a continuous variable. It will be performed using a repeated measures design on an intention-to-treat (ITT) basis, and a linear mixed effects regression by means of the restricted maximum likelihood (RML) method, controlling for age and sex. The “treatment by time” interaction will be calculated to determine possible differences between the study arms over time. The slope coefficient, representing the adjusted mean difference change, as well as its 95% confidence interval (95% CI), will be calculated. Hedge’s g statistic, as an effect size measure of between-group differences, will be calculated from the raw data. The rule of thumb for effect size interpretation will be 0.20 = small, 0.50 = medium, and 0.80 = large.

Secondary analysis will explore the effects achieved in the primary outcome at three-month follow-up, as well as in the secondary outcomes at post-intervention and at three-month follow-up, following the same analytical approach. Sensitivity analysis will assess the effects of missing data, which will be assumed to be missing at random and replaced by multiple imputations based on chained equations, including the main and secondary outcomes of all the waves––as well as routinely collected sociodemographic data. Other secondary analyses will explore reliable change and clinically significant change in quality-of-life improvements using the Jacobson and Truax method [63]. These classifications will be used to calculate the absolute risk reduction (ARR) and the number needed to treat (NNT); a 95% CI for each NNT will also be calculated. We will use a two-sided test with a 0.05 significance level. No corrections for multiple comparisons will be made for the primary analysis––because only one contrast will be made. Secondary analyses will be corrected for multiple comparisons by adjusting the significance threshold according to the Benjamini-Hochberg procedure [64].

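### Both treatments are delivered in groups, but the sample size and the stated models make no allowance for therapy-group clustering

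*Protocol article*

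**What the plan says.** **Delivery.** Under AIR + mindfulness: "The intervention will be administered by a clinical psychologist who is trained in and has experience in facilitating groups" for both components of that programme. Under Relaxation intervention: "The intervention will be administered by a clinical psychologist who is experienced with groups and is trained in relaxation therapy". The relaxation sessions open with an introduction of the group and regularly include members sharing their homework experiences. Among the strengths in the Discussion: "The fact that the intervention is delivered in a group format can generate a context in which the participants" are more engaged, with better adherence and more benefit as the expected result. The same paragraph names the relationship with the group as something that can itself change outcomes.

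**Sample size.** The inputs are an effect from a fibromyalgia trial, "with a moderate effect size (d = 0.60) at post-intervention", a two-sided 5% level, 80% power and about 15% dropout. The result is "a statistical power set at 80% in two-tailed tests, 42 patients per group are required", raised to 50 enrolled per arm. No group size, ICC or design effect appears.

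**Analysis.** The Data analysis plan specifies a repeated-measures, intention-to-treat comparison using "a linear mixed effects regression by means of the restricted maximum likelihood (RML) method, controlling for age and sex", with a treatment-by-time interaction. Secondary outcomes follow the same approach. Mediation uses ordinary least squares with bootstrapped indirect effects. Therapy group is mentioned in none of these.

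**The concern.** People who share a therapy group share a leader, a set of sessions and each other. After treatment their outcomes tend to be more alike than those of people in different groups, even though they were randomised one by one. The protocol relies on this mechanism when it credits the group context with extra benefit, but gives it no place in the statistics.

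Two things are at stake. If the analysis ignores groups, the variance of the treatment effect is understated, the confidence interval is too narrow, and the single primary test rejects a true null hypothesis more than 5% of the time. If the analysis allows for groups, the power falls below the figure given under Sample size. The first can be repaired by a model term. The second is a planning figure, and a later model term does not make it correct.

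**Working it through.** **Inputs from the protocol article (Sample size).** d = 0.60 in SD units, two-sided α = 0.05, power 80%, 42 evaluable per arm, 15% dropout, 50 enrolled per arm.

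**Inputs that are assumed.** Patients per group m = 8, 10 or 12, and ICC = 0.01, 0.05 or 0.10, the same in both arms. The document gives neither.

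**1. The plan's own figure.** For two independent means, n per arm = 2 × [(1.960 + 0.842)/0.60]² = 43.6, so 44; the t-test version gives 44.6, so 45. The stated 42 is close but slightly low. At n = 42 the standard error is √(2/42) = 0.218 and 0.60/0.218 = 2.75, so power = Φ(2.75 − 1.96) = 78.5% (77.6% by t-test). For dropout, 42/0.85 = 49.4, so 50. The step from 42 to 50 is used up by dropout, and no margin is left for clustering.

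**2. With clustering.**
- Design effect: DE = 1 + (m − 1) × ICC
- Effective n per arm: 42/DE
- Power of a test that allows for groups: Φ(0.60/√(2·DE/42) − 1.96)
- Type I error of a test that ignores groups: 2 × [1 − Φ(1.96/√DE)]

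Worked case, m = 10 and ICC = 0.05: DE = 1 + 9 × 0.05 = 1.45. Effective n = 42/1.45 = 29.0. Standard error = √(2 × 1.45/42) = 0.263, and 0.60/0.263 = 2.28, so power = Φ(0.32) = 62.7%. The standard error is understated by a factor of √1.45 = 1.20. Type I error = 2 × [1 − Φ(1.96/1.20)] = 10.4%.

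| m | ICC | DE | Effective n per arm | Power | Type I error if groups ignored |
|---|---|---|---|---|---|
| any | 0 | 1.00 | 42.0 | 78.5% | 5.0% |
| 8 | 0.01 | 1.07 | 39.3 | 75.7% | 5.8% |
| 10 | 0.01 | 1.09 | 38.5 | 75.0% | 6.0% |
| 12 | 0.01 | 1.11 | 37.8 | 74.2% | 6.3% |
| 8 | 0.05 | 1.35 | 31.1 | 65.8% | 9.2% |
| 10 | 0.05 | 1.45 | 29.0 | 62.7% | 10.4% |
| 12 | 0.05 | 1.55 | 27.1 | 59.8% | 11.5% |
| 10 | 0.10 | 1.90 | 22.1 | 51.4% | 15.5% |

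The last two columns describe different analyses: power is for a test that holds its 5% level, type I error for one that leaves groups out. All power figures use the normal approximation and treat the group variance as known, so they are somewhat optimistic when groups are few.

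**The case against.** **The analysis plan is not shown.** The article is a condensed account, and its Data Availability section refers to a separate statistical analysis plan. The Data analysis plan names fixed covariates but no random effects, not even a participant intercept, so a group term might be specified elsewhere. This stands as a limit on the model half of the point. It does not help the sample size, which is fully stated and assumes independence.

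**The ICC may be very small.** This is fair. At an ICC of 0.01 the loss is only about 3 to 4 percentage points, and type I error is about 6%. The direction is fixed for any positive ICC; the size is not.

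**Baseline adjustment could recover power.** In part. With an assumed baseline correlation of 0.5, 42 per arm gives about 89% before clustering, although the planning calculation does not use this. Group effects arise after randomisation, so baseline scores do not remove them. With group variance 0.05 and residual variance 1 − 0.5² = 0.75, the residual ICC is 0.05/0.75 = 0.067. With m = 10, DE = 1 + 9 × 0.067 = 1.6, power is about 71%, and type I error is about 12% if groups are ignored.

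**Stronger readings that the document does not support.** A reader might infer that one therapist runs each arm, so that therapist and treatment are confounded. The intervention sections do speak of a single psychologist, but that can be read as a required qualification, and the section on randomization and blinding refers to psychotherapists in the plural. A reader might also conclude that the Discussion's remark about the instructor's attention is wrong. That remark concerns non-specific attention, which a control with the same number and length of sessions does address; it makes no claim about differences between individual therapists. Finally, one could quote much lower power using degrees of freedom counted from groups. The number of groups is not stated, and with 8 degrees of freedom power is about 67% even at an ICC of zero, so much of such a drop would come from the chosen degrees of freedom rather than from correlation.

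**Conclusion.** The point holds in this form: treatment is given in groups in both arms, the document argues that the group context matters, the sample size assumes independent patients, and the stated primary and mediation analyses contain no therapy-group term. For any positive within-group correlation the consequences are an understated standard error, a type I error above 5% if groups are ignored, and power below 80%.

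The size rests on assumed group sizes and ICCs. For groups of 8 to 12 with 42 evaluable per arm, it runs from slight at an ICC of 0.01 to material at 0.05. The first 1.5 points of the power shortfall (80% to 78.5%) come from rounding in the sample size calculation and have nothing to do with clustering. The sample-size half is firm; the model half is subject to what the unseen analysis plan contains.

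**What to change.** - Record a therapy-group identifier for every participant from the first session. It is easy to capture during delivery and may not be recoverable afterwards.
- Add a random effect for therapy group within arm to the primary and secondary models, with Kenward-Roger or Satterthwaite degrees of freedom. If the analysis plan already does this, say so in the protocol. State how the mediation analysis handles therapy group.
- Restate the power under Sample size for the planned group size over an assumed ICC range, starting from the 78.5% that 42 per arm gives under independence.
- If an arm runs as a single group, or if one therapist delivers all sessions of an arm, state as a limitation that group or therapist effects cannot be separated from the treatment effect. No model term can then do so.

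**Cost.** One identifier, one model term and a rewritten power paragraph; no extra patients. Intervals will be wider and the stated power lower, because the change corrects the claim and does not restore 80%. With few groups the group variance will be estimated imprecisely.

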## Data Availability

In accordance with the International Committee of Medical Journal Editors (ICMJE), the data generated by this trial will be made available upon reasonable request to researchers (i) who provide a methodologically sound proposal and (ii) whose proposed use of the data has been approved by an independent ethical review committee. The data sharing plan includes all anonymized and fully deidentified participant data collected during the trial, as well as the study protocol, statistical analysis plan, and data dictionary with descriptive labels. Data will become available following each publication with no end date and for any analytical purpose that is related to achieving aims in the original approved proposal. The database will be encrypted and password protected. Passwords will be provided by the corresponding author to interested researchers who meet both conditions (i) and (ii).

## Abbreviations

AAQ-II: Acceptance and Action Questionnaire-II
AIR: Amygdala & insula retraining
CFS: Chronic fatigue syndrome
ERQ: Emotion Regulation Questionnaire
FFMQ-24: Five Facet Mindfulness Questionnaire
GAD-7: General Anxiety Disorder
ISI: Insomnia Severity Index
ME: Myalgic encephalomyelitis
MEF-30: Memory Failures of Everyday
MFIS: Modified Fatigue Impact Scale
PCS: Pain Catastrophizing Scale
PHQ-9: Patient Health Questionnaire
RCT: Randomized controlled trial
SCPGS: Spanish Chronic Pain Grading Scale
SF-36: Short Form Health Survey
